## Abstract

**Introduction:**

Multiple sclerosis (MS) is a progressive disease with a fluctuating and unpredictable course that has no curative treatment at present. One of its main characteristics is the variety of signs and symptoms that produce a high percentage of patients who present alterations in balance and gait during the development of the disease, decreased muscle strength, spasticity, or decreased pimax. Rehabilitative therapy, especially physiotherapy, is the main course of the treatment of these alterations using reflex locomotion and the Bobath concept as a form of kinesitherapy that activates the preorganized circuits of the central nervous system.

**Objective:**

The objective of this study is to evaluate the reflex locomotion and Bobath concept effects on balance, spasticity, reaction time, respiratory parameters, and lacrimal biomolecular markers.

**Methods and analysis:**

This is a randomized controlled trial on the effectiveness of two neurorehabilitation techniques in patients with multiple sclerosis conducted at the University of Salamanca. The research will take place at the Faculty of Nursing and Physiotherapy, University of Salamanca. The study will be conducted from June 2023 to June 2024. The reflex locomotion group will receive individual sessions of therapy (*n* = 27), and the Bobath concept group (*n* = 27) will receive the same number of sessions. Both groups will receive two sessions per week for 12 months. The measurement variables will be the Berg Balance Scale, the Tardieu Scale, the Cognitfit Program, Maximum Inspiratory Pressure, and Lacrimal Biomarkers.

**Ethics and dissemination:**

This study has been approved by the Ethics Committee of the University of Salamanca on March 2023 (ref: 896).

**Limitations:**

The main limitations of this study are the selection and number of patients, the delay in implementing the therapy within the initially scheduled period, inadequate sample collection, and inadequate sample processing.

**Trial registration number:**

ClinicalTrials.gov; identifier: NCT05558683.

## Highlights

- Examining the effectiveness of two physical therapy treatments in patients with multiple sclerosis through a randomized controlled trial could provide insight into which types of techniques are most effective for these patients.- Primary outcome variables will be measured objectively through validated and adapted tests/instruments, providing a valid basis for data interpretation.- Biochemical parameters will be measured at the Institute of Neurosciences of Castilla y León by qualified personnel trained in this type of measurement and not by the study team.

## Introduction

Multiple sclerosis (MS) is considered a chronic, multifocal demyelinating disease of the central nervous system (CNS). Its diagnosis is fundamentally clinical. The level of disability is rated using the Expanded Disability Status Scale (EDSS), a scale useful for measuring neurological disability (cerebral, cerebellar, pyramidal, brainstem, sensory, bowel, visual, and bladder functions) (1).

Given that sometimes drug treatment does not have the desired efficacy, some authors highlight the importance of physiotherapy (2) as an important part of the symptomatic and supportive treatment of people with MS since it induces improvement of the affected physiological functions occurred due to lack of physical activity and helps control some symptoms, such as spasticity, fatigue, and lack of balance (3).

The reflex locomotion (Vojta Method) and the Bobath concept are considered two variants of special interest in their approach (4–6).

The reflex locomotion created by [name] between 1950 and 1970 is based on the principle of reflex locomotion, so it is possible to reflexively trigger repeated motor reactions in the trunk and extremities from defined stimuli and from certain postures. The movement complexes that are activated are reflex crawling and reflex turning, producing numerous effects and benefits at a global level (7, 8).

The neurophysiological mechanisms of this reflex locomotion have recently been discovered. In their study, Sanz-Esteban et al. (9) concluded that the application of the therapy activates the basal ganglia, the putamen, the anterior cerebellum, and the thalamus. These structures play an essential role in motor actions. In a recent study (10), stimulation of the chest area was used in the oscillation reflex coordination complex, showing activation of cortical areas such as supplementary motor areas (SMA) and premotor areas (PMA; Brodmann areas BA6 and BA8), which are areas in charge of movement planning, regulation, and execution, as demonstrated by Martínek et al. (11).

In addition, it has been shown that reflex locomotion produces an involuntary contraction of the abdominal musculature measured by electromyography (12). In other studies by Laufens et al. (13, 14), we can verify the great benefits obtained by combining reflex locomotion with Laufens electromyographic results in the improvement of fatigue and muscle strength, reporting improvements of up to 68.4% in cerebellar functions and 78% in lower limb strength.

However, the Bobath concept is a valid and recognized option in the treatment of patients with neurological disorders and, therefore, of those diagnosed with MS. It was developed by Karel and Berta Bobath. The Bobath concept is defined as a problem-solving approach in the evaluation and treatment of people with altered neuromotor function, becoming a valid tool as part of the comprehensive treatment of patients with MS (15).

Castelli et al. show the positive impact of the application of the Bobath concept on balance, postural control and indirect adaptive neuroplasticity index in people with multiple sclerosis (6).

It is important to mention that there are other relevant studies with butolinic toxin treatment combined with reflex locomotion and the Bobath concept to improve spasticity in patients with multiple sclerosis (16).

Through this concept, active movements are carried out, which requires the participation of the patient, where the individual fulfills the motor, sensitive, and cognitive functions; the executed tasks lead to stability and mobility, incorporating knowledge of motor learning, biomechanics, motor control, and brain plasticity depending on the activity that requires recovery after brain injury (17).

Also relevant is the appearance of abnormal postural and movement patterns due to the release of abnormal postural reflex activity (18).

We must highlight that reflex locomotion and the Bobath concept are shown to be one of the most widely used therapies in the rehabilitation process of potentially altered variables such as spasticity, reaction time, muscle strength, balance, and pimax during the course of diseases such as multiple sclerosis. However, to date, there has been no study that has evaluated the effectiveness of both therapies in a population diagnosed with multiple sclerosis. In addition, most studies demonstrate the clinical improvement experienced by people with multiple sclerosis; however, the reason for this clinical improvement is not explained. Therefore, studies like ours could be a therapeutic tool that would facilitate the direct activation of innate patterns in the central nervous system. This would allow us to activate partial movement patterns and use them to achieve better postural control, stabilization, improved support, and coordinated phasic movement. Although the relationship between the application of reflex locomotion and the activation of central nervous system structures during the development of multiple sclerosis has been demonstrated, it is interesting to consider its combined use with other therapies.

One of the tools used as part of the exploratory analysis in clinical practice that refers to the state of health of the disease and its evolution is the multiple sclerosis response biomarkers. In this research project, we will analyze biomarkers in tear fluid, which would allow the progression of the disease to be quickly and inexpensively deciphered. Tear fluid constitutes a biological sample related to the nervous system and is easily obtained, constituting a very interesting source of study for the detection of biomarkers of neurodegeneration (19–21).

There are few comparative studies on the effectiveness of reflex locomotion vs. the Bobath concept as rehabilitative therapies in people with MS, and none to date have analyzed in parallel the expression of tear biomolecular markers that could participate in the myelination process, balance, respiratory parameters, spasticity, and reaction time. Hence, we highlight the relevance of our hypothesis while proposing a new methodology in physiotherapy (22, 23).

## Hypotheses

Reflex locomotion and the Bobath concept are two techniques used in rehabilitation for the evaluation and treatment of people with disorders of function, movement, and postural control as a result of a lesion in the central nervous system. To date, there are few comparative studies on the effectiveness of both techniques as rehabilitation therapies for people with multiple sclerosis. None of these studies have analyzed whether the application of these therapies entails a modification of the levels of certain tear substances indicative of processes of myelination, balance, respiratory parameters, spasticity, and reaction time that could act as biomarkers of disease progression.

Our hypothesis is that the application of reflex locomotion in subjects with MS causes a greater improvement in their physical condition and, in general, in their quality of life compared to the Bobath method. This improvement is justified because the first (reflex locomotion) modifies the activity of the central nervous system (CNS), while the second (Bobath concept) acts only at the muscular level. Likewise, we propose that the improvement can be monitored by an alteration in the levels of certain compounds extracted from the tears of the subjects, such as sphingomyelin, which have previously been described as tear biomarkers in the etiology of MS (24).

## Methods and analysis

### Study design and setting

A double-blind randomized controlled trial will be conducted at the Faculty of Nursing and Physiotherapy, University of Salamanca (Spain), according to the consolidated standards of reporting trials (CONSORT) statement (25). The current treatment protocol is described according to the recommendations of SPIRIT (26).

The protocol of this trial received the approval from the Ethics Committee of the University of Salamanca (record number 896) and will be conducted according to the Declaration of Helsinki. The clinical trial was registered at ClinicalTrials.gov (registration number NCT05558683).

The study will be conducted between 1 July 2023 and 1 June 2024 in the Faculty of Nursing and Physiotherapy at the University of Salamanca.

### Participants: inclusion/exclusion criteria

A total of 50 participants will be recruited from the general population with a diagnosis of multiple sclerosis according to the Expanded Disability Status Scale who attend their neurology consultation at the University Hospital of Salamanca. The participants in this study will be adults, aged between 20 and 60 years, of both sexes. All subjects will sign a written informed consent form before any data are collected.

Exclusion criteria will be as follows: (1) Participants with multiple sclerosis with an EDSS scale score equal to or higher than 7.0 will be excluded, (2) Pregnant women, (3) Oncology patients, (4) Non-acceptance and non-signing of the informed consent, (5) Refusal to participate in the study, (6) Patients with severe cognitive impairment that does not allow them to understand the development of the study, (7) Patients with cardiovascular instability, (8) Patients who do not complete at least 75% of the scheduled sessions, (9) Patients who do not present any of the contraindications contemplated for reflex locomotion.

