**Figure 1 F1:**
[figure not shown]
Neurorehabilitation treatment according to Vojta's reflex locomotion.

**Who will provide:** All interventions will be performed by a physiotherapist with more than 20 years of experience in treating people with neurological problems.

**How:** The physiotherapy technique will be performed individually twice a week for a duration of 45 min for a period of 12 months (22, 23).

**Where:** All sessions will be conducted at the Faculty of Nursing and Physiotherapy, University of Salamanca (Spain).

**When and for how long:** Participants will receive two sessions per week for 12 months. The average duration of the session will be ~45 min. The same weekly schedule will always be respected for each of the participating subjects.

**Tailoring**: Due to the nature of the intervention and the wide heterogeneity of the subjects, the sessions will be individualized and tailored to each subject.

**How well (planned):** Therapy supervision will be provided through weekly meetings between therapists and investigators. In addition, a thorough control of the subjects' attendance at the sessions will be carried out.

**How well (actual):** Not applicable.

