### Allocation and randomization

Participants will be randomly assigned to one of the two intervention groups, namely, the reflex locomotion group or the Bobath therapy group.

Concealed allocation will be performed with a computer-generated random table of numbers created by an external statistician who will not be involved in the analysis or interpretation of the results. Individual, sequentially numbered tokens will be prepared for the random assignment. The cards will be placed in sealed, opaque envelopes, which will be opened by an external evaluator. The assignment to treatment will be revealed to the participants after the initial results are collected.

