#### Risk factor 2: delay in implementing the therapy within the initially scheduled period

Although different factors may delay the implementation of planned therapies, one of the most relevant could be the appearance of MS attacks in evaluated patients during the assay. This would probably lead to a delay in taking samples and carrying out the proposed therapy. To counteract this circumstance, a new subject in the study and/or an extension in project duration may be considered depending on the time risk.

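### Exclusion criterion (8), completing fewer than 75% of sessions, can only be applied after randomisation, so as written it removes randomised participants and could bias the arm comparison

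*Protocol article*

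**What the plan says.** Under Participants: inclusion/exclusion criteria, the list opens with "Exclusion criteria will be as follows" and gives as item (8) "Patients who do not complete at least 75% of the scheduled sessions". It stands among items that can be checked at screening, such as EDSS score, pregnancy and consent.

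Under Allocation and randomization, "Participants will be randomly assigned to one of the two intervention groups", and "The assignment to treatment will be revealed to the participants after the initial results are collected". Treatment therefore follows allocation. Under Interventions, both arms have the same schedule: "Participants will receive two sessions per week for 12 months". Outcomes are measured at baseline and at 3, 6 and 12 months (Outcomes). Statistical methods plans a repeated-measures ANOVA of pre/post by group.

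Under Limitations, Risk factor 2, the document names "the appearance of MS attacks in evaluated patients during the assay" as a likely cause of delay to sampling and therapy, and answers that "a new subject in the study and/or an extension in project duration may be considered depending on the time risk".

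**The concern.** Session attendance over a year is not an eligibility criterion. It is a consequence of what happens after allocation. Listing it as an exclusion means that the only people it can act on have already been randomised.

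In MS, attendance plausibly follows fatigue, relapse, progression and tolerance of the treatment, all of which relate to the balance, spasticity and respiratory outcomes. The two arms also receive clearly different hands-on treatments: pressure stimulation in set positions in one, active facilitation with varied equipment in the other. The share removed, and the kind of patient removed, could therefore differ by arm.

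The comparison would then be between those who kept attending and no longer between the groups that randomisation formed. If excluded participants also stop being assessed, their outcomes will not exist, and no later analysis plan can restore them.

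**Working it through.** **Step 1. When can criterion (8) be known?** Two sessions a week is the document's figure; the number of weeks depends on the reading.

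- 52 weeks (assumed for 12 months): 2 × 52 = 104 sessions; 0.75 × 104 = 78. A participant is certain to fail only after missing 104 − 78 + 1 = 27 sessions. Someone who attends none reaches that in week 14.
- 1 July 2023 to 1 June 2024 (Study design and setting): 336 days = 48 weeks; 2 × 48 = 96 sessions; 0.75 × 96 = 72. Certain failure needs 96 − 72 + 1 = 25 missed sessions, in week 13 at the earliest.

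On either reading the criterion cannot be met at screening, and for most participants it is settled much later than three months.

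**Step 2. What removal does to one arm.** Let x be the share excluded and D the gap in mean change, attenders minus non-attenders, in SD of change. The all-randomised mean is (1 − x) × attender mean + x × non-attender mean. The retained mean is the attender mean. Hence

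retained mean − all-randomised mean = x × D.

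If non-attenders do worse (D > 0), that arm's own change is inflated.

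**Step 3. What it does to the difference.** Bias in the difference = x₁D₁ − x₂D₂, for arms 1 and 2. The document gives no value for x or D, so the following are assumptions:

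- Equal x and equal D in both arms: bias = 0.
- x₁ = 0.25, x₂ = 0.05, D = 0.5 in both: 0.125 − 0.025 = 0.10 SD.
- x₁ = 0.25, x₂ = 0.05, D = 1.0 in both: 0.25 − 0.05 = 0.20 SD.
- Shares swapped between arms: −0.10 and −0.20 SD.

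**Step 4. Check by simulation.** Settings: 27 per arm, no true effect, change scores with SD 1, 20,000 runs, two-sample t test at two-sided 0.05. Completion is a latent variable correlated with change. Exclusion shares and correlations are assumptions.

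| Excluded, arm 1 vs arm 2 | Correlation of completion with change | Mean difference (SD) | Type I error |
|---|---|---|---|
| 20% vs 20% | 0.5 | 0.00 | 4.8% |
| 30% vs 10% | 0 | 0.00 | 5.0% |
| 30% vs 10% | 0.3 | 0.09 | 6.1% |
| 30% vs 10% | 0.5 | 0.15 | 7.5% |
| 40% vs 0% | 0.5 | 0.32 | 16.9% |

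The simulation agrees with the algebra. There is no bias when exclusion is balanced or unrelated to outcome, and bias grows as exclusion becomes unbalanced and related to outcome.

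**The case against.** **The analysis population may be defined elsewhere.** An article commonly leaves this to the full protocol or SAP, so the absence of an intention-to-treat statement is no defect. That is right, and the point does not rest on it. It rests on a rule that the document does state. It is also fair that the rule calls these patients excluded without saying that their assessments stop or their data are dropped. Removal is the natural reading of an exclusion criterion, and nothing in the article overrides it.

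**The bias may be nil.** This stands. Balanced exclusion with equal gaps leaves the difference unbiased, and if the Bobath arm lost more poor responders the bias would run against the trial's own hypothesis. A reader might infer that the result must be over-optimistic for reflex locomotion; the document does not support a direction.

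**Relapsing patients.** A reader might infer from Risk factor 2 that participants with an MS attack are swapped out. The text does not say so. It concerns delay, is conditional, offers an extension as an alternative (which points towards keeping delayed patients), and says nothing about dropping anyone's data. A new subject could be an addition. What remains is an ambiguity: the text does not say that the relapsing participant stays in.

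**The 20% loss.** A reader might take the loss allowance under Power and sample size as the number this rule would remove (0.20 × 54 = 10.8, about 11). Nothing there links that general allowance to criterion (8).

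**Conclusion.** The point holds for criterion (8). As written, it excludes randomised participants on a post-randomisation event that may depend on disease course and assigned therapy. This is a stated rule that can undo the randomised comparison, and it should be corrected before assessments are lost.

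The size of the bias cannot be derived from the document. Under the assumptions shown it runs from zero to 0.10–0.20 SD in either direction, and to about 0.3 SD in the most unbalanced case simulated. Each arm's own change is inflated whenever non-attenders do worse, even where the difference is not biased. The session thresholds (78 of 104, or 72 of 96) depend on which duration is meant, but the conclusion does not.

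The sentence on MS attacks needs clarification only; it is not evidence that relapsing patients are removed.

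**What to change.** - Delete criterion (8) from the exclusion list.
- State that all randomised participants are assessed at 3, 6 and 12 months whatever their attendance, and are analysed in the arm to which they were assigned.
- Keep the 75% threshold only as the definition of a supportive per-protocol analysis, and state the number of scheduled sessions it refers to.
- As a secondary clarification in Risk factor 2, state that a participant with an MS attack stays in follow-up and in the analysis as randomised, and that any new subject is an additional randomised participant and not a substitute.

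The cost is a change of wording plus the effort of keeping assessment visits for low attenders. The estimate will be somewhat diluted by participants who received little therapy. Some low attenders may still miss assessments, so the change reduces the risk of bias without guaranteeing its absence. No treatment rule is altered.

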### Limitations

#### Risk factor 1: selection and number of patients

A total of 50 patients diagnosed with RRMS will be selected. They will come from Salamanca's capital and its province. Considering that the MS Care Unit of Salamanca Hospital evaluates more than 300 patients diagnosed with MS disease in general, an initial screening will be carried out to select 50 individuals who could benefit from these therapies. Individuals belonging to different MS associations from nearby provinces to Salamanca (Salamanca) may also participate if there is a need to select additional participants in this assay.

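### Exclusion criterion (9) is worded in the wrong direction, and the eligibility section and the Limitations name different MS populations

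*Protocol article*

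**What the plan says.** The section on participants and eligibility introduces a numbered list with "Exclusion criteria will be as follows". Item (9), the last, is "Patients who do not present any of the contraindications contemplated for reflex locomotion".

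The allocation section then states: "Participants will be randomly assigned to one of the two intervention groups, namely, the reflex locomotion group or the Bobath therapy group". It makes no exception for people who should not receive one of the two therapies.

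On the disease itself, the eligibility section recruits people "with a diagnosis of multiple sclerosis according to the Expanded Disability Status Scale". Its only further limit tied to the disease is item (1): "Participants with multiple sclerosis with an EDSS scale score equal to or higher than 7.0 will be excluded". No MS course is named there.

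Under Limitations, Risk factor 1, the article says: "A total of 50 patients diagnosed with RRMS will be selected". It sets these 50 against the more than 300 people with MS of any kind who are seen at the hospital's MS unit.

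**The concern.** An exclusion criterion should describe a reason to keep a patient out. Item (9) describes a patient who is suitable for reflex locomotion and lists that suitability as the reason for exclusion. Taken at its word, the trial would randomise only people with a contraindication to one of its two therapies.

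Eligibility criteria are what screening staff, monitors and later readers check enrolment against. With the rule reversed, a properly enrolled patient counts on paper as a protocol deviation, and an improperly enrolled one counts as compliant.

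The second matter is narrower. If one section admits MS without regard to course and another says that the selected patients have RRMS, the article does not fix a single target population. That leaves open who may be enrolled and to whom the comparison applies.

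**Working it through.** No formula or stated figure is involved. The check is a literal reading of the rules, set side by side.

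**Item (9).**

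1. Let E be the people who meet the age and diagnosis requirements and are not removed by items (1) to (8). Let C be those with at least one contraindication to reflex locomotion.
2. Item (9) as printed excludes the people not in C. The eligible set is therefore E ∩ C.
3. The evident intention is to exclude the people in C. The eligible set would then be E ∩ (not C).
4. These two sets do not overlap, and together they make up E. Every member of E is thus classified in opposite ways by the two readings.
5. The negative phrasing is not the fault in itself. Item (8) also uses a negative, but there it describes a shortfall (too few sessions completed), which fits an exclusion heading. Only in item (9) does the negative describe a suitable patient.
6. Under the allocation section, every enrolled participant may receive reflex locomotion. If the eligible set is E ∩ C, then everyone allocated to that arm has a contraindication to it. The literal rule and the allocation rule cannot both stand.
7. No other section of the article restates or corrects item (9).

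The size of E ∩ C cannot be given, because the article does not say what the contraindications are. If all of them were already covered by items (1) to (7), E ∩ C would be empty and nobody could be enrolled. If some were not, those are the people who would remain.

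**MS course.**

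| Place in the article | Population stated |
|---|---|
| Eligibility section | MS, age 20 to 60, EDSS below 7.0, no course named |
| Limitations, Risk factor 1 | RRMS, 50 patients |

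RRMS is a subset of MS, so the second population can sit inside the first. The two still differ for one group: people aged 20 to 60 with another MS course and an EDSS below 7.0. The eligibility section admits them, and the Limitations statement does not.

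The number involved depends on the share p of RRMS among otherwise eligible patients, which the article does not give. Assuming that 50 patients are enrolled in the same mix, 50 × (1 − p) are affected. That runs from 0 (p = 1) to 50 (p = 0), and each 10 percentage points of non-RRMS patients corresponds to 50 × 0.10 = 5 participants. Nothing in the article narrows the range.

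**The case against.** The strongest reply is that nobody running this trial could follow item (9) literally. It reads like an inclusion statement placed in the wrong list, and the design makes its intended meaning plain. Other safeguards also remain: items (1) to (3), (6) and (7) still exclude high EDSS scores, pregnancy, oncology patients, severe cognitive impairment and cardiovascular instability. The therapy is given by a very experienced physiotherapist, and the ethics section describes the risk as minimal. This stands as far as consequences go. A reader might infer from the wording that at-risk patients will be enrolled and suitable ones turned away; the article gives no sign that this would happen in practice. What remains is that the written rule is wrong and nothing corrects it.

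On MS course, it is fair to say that RRMS is nested in MS, and that the Limitations may simply give a narrower account of who will be chosen. But nesting does not remove the mismatch: the eligibility criteria do not contain the restriction that the Limitations state.

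Two further inferences are tempting but not supported:

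- **The diagnosis wording.** The eligibility section ties diagnosis to the EDSS, while the Introduction says "Its diagnosis is fundamentally clinical" and treats the EDSS as a disability rating. A reader might conclude that the diagnostic standard is wrong. This is loose phrasing that changes nobody's eligibility: the patients are those "who attend their neurology consultation at the University Hospital of Salamanca", and the EDSS is used properly as a limit in item (1).
- **The missing list.** A reader might fault the article for not listing the contraindications. A journal article may leave that detail to the full protocol, so its absence is not an error.

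**Conclusion.** The point holds as an error of wording and an internal inconsistency, not as a flawed design choice. Item (9) is reversed relative to its heading and conflicts with the allocation section. On paper it reverses the status of every candidate who passes the other criteria. Its practical effect on enrolment is probably small, assuming that staff read it as evidently intended, but a safety-related eligibility rule should not depend on staff reading past its text.

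The mismatch over MS course is real and secondary. Its size cannot be determined from the article.

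Neither matter touches the sample size, the power or the planned analysis.

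**What to change.** Reword item (9) so that it agrees with the exclusion heading and with the allocation of any participant to either therapy. Alternatively, keep its sense and move it to the inclusion criteria.

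State one target population, including whether MS course restricts entry, in the eligibility section, and make Limitations, Risk factor 1 match it. Which population is meant is for the investigators to say; the two sections need only be reconciled.

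The cost is about one sentence in each place. Nothing has to be recalculated. If screening has already begun, it would be sensible to confirm which reading of item (9) and which MS population were applied, and to report that with the results.
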